## Abstract

In epidemic and pandemic contexts, such as that of COVID-19, epidemiological changes are continuous, and many people do not have access to accurate, up-to-date information. In this context, social learning can be an advantageous survival strategy. We investigate whether people remember and communicate information attributed to someone prestigious more often than that attributed to family members, politicians, and people with experience in public health. The experimental phase will include a recall stage and an information transmission stage, which will be based on a fictitious text containing an opinion about a drug treatment for COVID-19. There will be four versions of the text, and each participant will be assigned one of these versions for the investigation. The participants will be instructed to read the fictional story and then complete a distraction exercise. Subsequently, a recall test will be performed, where they will be asked to recount the story as accurately as possible. The second stage of the experiment is aimed at testing the transmission of information where we will conduct a linear chain transmission experiment, where eight chains of four participants will be used for each story. They will be asked to write down their recollection of the material. This text will undergo spelling error correction and then be sent to the next participant in the chain through the platform. At the end of the experiment, there will be a self-reporting questionnaire for the participants; this allows for triangulation of the data.

## Introduction

In epidemic and pandemic contexts, such as that of COVID-19, there is a rapid rate of epidemiological change, and people do not always have access to accurate information [1]. In the early stages of such outbreaks, individuals need to make quick and important decisions on how to act amidst a large flow of incomplete and uncertain information [2]. Social learning can present itself as an advantageous survival strategy in such conditions [3].

The literature on cultural evolution has shown that, in the context of uncertainty, people need to select not only the information types (content) but also the information sources (models) [1–8]. Thus, in the context of a pandemic, learning from a model and attaining an above-average amount of information can be highly adaptive [3]. Recent evidence has shown that the source of information transmission in the pandemic context exerts considerable influence on people’s behavior [7, 9]. Therefore, different role models, such as family members [10], politicians [7], and the most prestigious individuals among the population [11], can influence how information is reproduced and transmitted. Of the existing set of role models that can influence information transmission, the prestigious type is very interesting. Henrich and Gil-White [12] argued that the evolution of prestige emerged through selective pressure to identify individuals within a group with “above-average” knowledge or skills, to learn from them. This would have led to information acquisition that increased aptitude. In other words, based on this theory, individuals who are more skilled within a certain domain knowledge tend to acquire prestige [12].

Individuals who enjoy prestige can be identified through factors such as personality, appearance, and material possessions. (first-order cues), as well as by the attention they receive from others (second-order cues), because prestigious individuals receive more attention within a population [12, 13]. According to the theory of the evolution of prestige, prestigious individuals can be influential even outside their domain of expertise [12].

In addition to influencing the transmission of information, the theory of evolution of prestige also implies that information from such individuals would be more memorable. The literature on adaptive memory has already provided evidence that certain pieces of information are remembered more than others [14–16]. In this sense, Henrich and Gil-White stated that, throughout the evolution of our psychology, a series of increasingly complex biases have shaped our minds [12]. However, the biases involved in the empirical studies on adaptive memory are mostly related to content or frequency of information [15, 17–19]; and to date, few investigations have been conducted within this theoretical background to determine the involvement of model biases. For instance, the study by Berl et al. [20], despite having been carried out with the aim of investigating the transmission of information, demonstrated that the prestige bias plays an important role in remembering. As predicted by Henrich and Gil-White [12] and with new evidence suggesting the role of prestige bias in human memory [20], it is possible that, overall, the prestige bias is active during both information transmission and recall in a context of uncertainty.

The COVID-19 scenario presents itself, then, as a large global experiment, with great potential for investigating how the prestigious role model may influence the recall and transmission of information and, consequently, influence human behavior. We intend to answer the following questions: [i] In a pandemic scenario, does a prestigious role model exert greater influence on information transmission than political and family role models and role models with expertise? [ii] In a pandemic scenario, does a prestigious role model elicit more information recall than political and family role models and role models with expertise?

## Hypotheses

**Hypothesis 1**: The transmission of information related to COVID-19 is strongly influenced by a source who possesses prestige.

*Prediction*: Information related to COVID-19 that is attributed to someone with prestige (digital influencers) is transmitted more often than the same information attributed to political role models, role models with public health expertise, and family members.

According to Henrich and Gil-White’s [12] theory, prestige is based on the merit that other people confer on certain individuals, which promotes greater admiration from others and a desire to be close. The "status" involved in this is proportional to the amount of attention received. Thus, as an individual receives more attention, their status will be higher [10]. The assumptions of the theory are as follows: [i] qualified individuals have a higher status; [ii] older individuals tend to obtain more prestige than younger individuals; [iii] individuals with perceived skill/knowledge receive privileges and are exempted from certain social obligations; [iv] people preferentially mirror qualified/successful individuals; [v] prestigious individuals are influential even beyond their domain of expertise; and [vi] prestigious individuals are more memorable.

Jimenez and Mesoudi [13] gathered existing evidence in the literature on prestige bias and added to their initial predictions, including the following: [i] prestigious individuals tend to be successful in domains that are currently important to a social group or that were valued in the recent past; [ii] prestigious individuals only achieve social influence when their domain of prestige is currently valued by a social group; [iii] the positive association between perceived success and prestige will be greater than the positive association between actual success and prestige; [iv] a more positive correlation between prestige and success indicates that more people will employ social learning with prestige bias; [v] prestigious individuals will be mirrored more often when the variation in knowledge/skill within a group is larger; [vi] prestige bias across domains occur more often when cues are not as evident within the domain tested than when those cues are clear; [vii] prestige bias across domains occur when there are general traits, which make people successful across domains [13].

To identify individuals who hold prestige and thus select the information to be reproduced, learners can evaluate different individuals’ competence within a given domain and then choose the best individual to follow. However, this can be very time-consuming and costly for survival. For this reason, learners use “shortcuts” called prestige cues to make inferences about the individuals’ characteristics such as appearance, personality, generosity, material possessions, (first-order cues), or they rely on the behavior of other social learners (second-order cues). Both can be useful for acquiring potentially adaptive information; conversely, they can also lead to unhelpful or maladaptive behavior [13].

First-order cues are based on the fact that these shortcuts generally have a positive association with competence in important domains. Nevertheless, this identification is subjective, as it depends on the social learners’ values as well as their social group. They are less cognitively demanding and, therefore, quite advantageous, but they may not be fully reliable. In contrast, second-order cues, are related to the fact that individuals pay more attention to, want to be near, and mirror individuals who are competent. Consequently, social learners can use other individuals’ behavior to select which role models to learn from. The advantage of these cues is that they are more difficult to falsify (unlike first-order cues) and can be updated regularly [13].

Recently, Berl et al. [21] developed a valid, reliable scale to assess individual prestige. The scale is based on three central components: position, reputation, and information. Position concern a given individual’s place in the social hierarchy, and it is based on three dimensions: wealth, high social status, and power (or influence). Reputation involves the individual’s social opinion and esteem; the latter represents the overall social evaluation of an individual in a particular position or function, which usually involves social and cultural values. Finally, information is composed of items relative to education and intelligence, or the value that society gives to those who demonstrate more knowledge about a certain subject [21]. This last component is also based on Henrich and Gil-White’s [12] theory that individuals can gain prestige by presenting desirable skills and knowledge within a given social group.

Prestige bias allows individuals to acquire information quickly and is less costly in a new environment, thus increasing the chances of acquiring potentially more adaptive information [12]. Atkisson et al. [22] investigated this through an experiment in which participants designed arrowheads and tried to maximize hunting success; this was measured in caloric return. Their main findings revealed that participants learned preferentially from prestige models, defined as models that others spent more time looking at, and that prestige information and success-related information were used to the same degree. Thus, their results support the important role that prestige bias plays in social learning [22].

Moya et al. [1] noted that in a context such as the COVID-19 pandemic, in which epidemiological and social changes were rapid and abrupt, the source transmitting information can exert great influence on the information that people will reproduce. Recent evidence shows us that the existence of social bubbles on social media platforms such as Twitter allows for false and true information about COVID-19 to be shared in the same proportion; additionally, this conformity may be associated with ideological issues and the person transmitting the information [9]. In light of this information and the theory of the evolution of prestige, we believe that people will select sources with social prestige to reproduce and transmit information about COVID-19.

**Hypothesis 2**: Recall of information related to COVID-19 is strongly influenced by a source that possesses social prestige.

*Prediction*: Information related to COVID-19 attributed to someone of prestige (digital influencers) is transmitted more often than the same information attributed to political role models, role models with public health expertise, and family members.

The way our memory works demonstrates how our ancestral psychology has evolved [23]. In the theory of prestige evolution proposed by Henrich and Gil-White [12], human memory has evolved into an increasingly well-organized and specialized set of biases. Prestige biases emerge from this evolved social learning psychology and may be influential, along with the mode of transmission, in information memorization [12]. For example, the empirical study of cultural transmission by Berl et al. [20] found evidence that prestige bias has significant effects on the information that people can remember. However, it did not examine whether this is also the case in unstable settings [such as the COVID-19 setting]. Jimenez and Mesoudi [24] also tested whether information provided by prestige models is better remembered over generations than information provided by low-prestige sources. The authors did not find sufficient evidence to support this hypothesis. Based on these results, and unlike the theory of prestige evolution, they assumed that it would not affect the recall of information along the transmission chains [24]. However, besides not being a specific memory experiment, the authors addressed something stable in daily life (the use of the tablet in the school environment). Furthermore, they also acknowledged the possibility that their manipulation of prestige did not adequately cover the way prestige works in everyday life. Therefore, it is unclear whether the result derived is due to the domain studied or due to methodological limitations, or whether prestige actually has no effect on recall.

We intend to properly control our experiment by clearly explaining to the participant the characteristics that confer prestige on the source of information. These characteristics are based on the scale and prestige cues developed by Berl et al. [21] to measure individual prestige. We will also use political, knowledgeable, and familiar sources who do not have prestige but are role models who exist in the real world. This will allow us to investigate whether prestige can, in fact, influence the flow of information within a pandemic context.

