#### Selection of the information used

Since information about COVID-19 has been in wide circulation throughout the population for almost two years, we will not use data pertaining symptoms and actual forms of prevention, as there is a risk of bias. Therefore, we will create fictitious information appropriate to the context. To select our prestigious role model, we considered the characteristics described in the scale developed by Berl et al. [21] to assess how people attribute prestige. These characteristics are based on social status and esteem, influence, and knowledge of a certain subject. As social media played an essential role in the pandemic scenario, mainly due to isolation measures [27], and personalities such as digital influencers gained a lot of notoriety, they serve as ideal examples for the prestigious role model. In this case, we consider digital influencers to be people who receive a significant amount of attention (the more followers they have, the greater their engagement and popularity) and have a prominent social status, expertise within their niche, and influence beyond that niche.

For the decision of the other models to be used (to be compared with the prestigious role model), we selected a role model who had knowledge on the subject of public health, but no prestige, to assess whether prestige is in fact more influential than expertise, in this scenario. For the other role models, we used a study carried out by Hornsey et al. [28], where it was stated that there are psychological roots behind our attitudes of accepting or rejecting scientific information. Six roots are then described: ideologies, vested interests, conspiracy worldviews, fears and phobias, expression of personal identity, and social identity needs. Conceptually, these roots are distinct; in practice, however, they can overlap [28]. We selected models that may have behaviors and attitudes that reflect the overlapping of these roots, such as politicians, who share the same ideologies and interests; family members, who, along with previous roots, also have the same worldviews, while also possibly validating opinions related to personal fears and phobias.

Furthermore, empirical studies have shown how politicians’ opinions are taken into account in decision-making during a pandemic [7]. Recent studies also reveal that family care is a human priority [10], so it is quite plausible for people within the family to act as role models.

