We will ensure that the selected models do not contrast with the ideologies of each participant, they are unnamed, and they are in line with the political positions and personal tastes of each reader, which is clear in the texts (Table 1).

**Table 1 pone.0281991.t001:** Models used in the elaboration of the text to carry out the recall experiments and transmission of information about COVID-19.

Role Models	
Prestigious	Digital influencer with many followers and considerable influence that the participant follows and admires
Political	Politician
Experience/Knowledge	Physician
Parental	Family member (one who is closest to the participant)

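### The comparators are declared to have no prestige, which conflicts with the plan's own prestige scale for the physician and politician, and no listed item checks how prestigious the assigned source was seen to be

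*Protocol article*

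**What the plan says.** The Protocol article asks whether a prestigious source is better recalled and transmitted than political, family and expert sources. Under Hypotheses, in the rationale for Hypothesis 2, it says of the comparators: "We will also use political, knowledgeable, and familiar sources who do not have prestige". Under Selection of the information used it describes the expert as "a role model who had knowledge on the subject of public health, but no prestige".

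The same Hypotheses section sets out the prestige scale that the plan adopts, with three components: position, reputation and information. Of position it says "it is based on three dimensions: wealth, high social status, and power (or influence"; of the third component, "information is composed of items relative to education and intelligence". Reputation covers social opinion and esteem. The prestigious model was chosen on this scale: "These characteristics are based on social status and esteem, influence, and knowledge of a certain subject". Table 1 defines that arm as "Digital influencer with many followers and considerable influence that the participant follows and admires" and names the comparators as a politician, a physician and the participant's closest family member.

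The Recall stage section lists the data collected from participants. A baseline form covers demographics, political inclination and religion. Five self-report topics follow: trusted sources, main information sources, own COVID-19, family COVID-19 and vaccination. The Data analysis section enters the four-level source label as the only fixed effect.

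**The concern.** Both hypotheses concern prestige, but what is randomised is a source label. The label stands in for prestige only if the influencer is seen as clearly more prestigious than each comparator. The plan settles this by declaration, and for two of the three comparators the declaration goes against its own definition. It also describes the recognition of prestige from first-order cues as subjective and dependent on the learner's values and group, so a declaration cannot replace a check.

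The plan itself shows what is at stake. It says that an earlier transmission study with a null result is hard to interpret, partly because its authors acknowledged that "their manipulation of prestige did not adequately cover the way prestige works in everyday life". A null result here would be open to the same doubt.

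**Working it through.** **Step 1: the comparators against the scale**

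| Source | What the plan declares | What its scale credits | Result |
|---|---|---|---|
| Politician | no prestige | power or influence, status | conflict |
| Physician | knowledge, no prestige | education, valued knowledge, status | conflict |
| Family member | no prestige | possibly esteem only | unverified, not contradicted |

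Two further statements point the same way. The Introduction says that people skilled in a domain tend to acquire prestige; in a text about a COVID-19 drug, the physician is the source from within the domain. Elaboration of the texts says that prestige-conferring characteristics will be described for the role models, in the plural.

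**Step 2: is perceived prestige among the listed items?** No. The trust question is the nearest, but it asks about kinds of source in general, not about the source in the text that the participant read.

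**Step 3: reproduce the plan's sample size.** Inputs from Sample size: odds ratio 1.81, baseline probability 0.1, R² = 0, normally distributed covariate, α = 0.05 with z = 1.64 (one-sided), power 0.95. The method is the Wald test for one N(0,1) covariate in logistic regression, by the Demidenko formula with variance correction:

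N = (z₀.₉₅·√v₀ + z₀.₉₅·√v₁)² / b²

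- b = ln 1.81 = 0.593
- v₀ = 1/[μ(1−μ)], where μ = 0.1125 is the mean event probability over the covariate, so v₀ = 10.02
- v₁ = 11.22, the slope's entry in the inverse information matrix
- N = (1.645 × 3.165 + 1.645 × 3.350)² / 0.352 = 326.2, rounded up to 327

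This matches the plan, and the figure is not in dispute.

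**Step 4: illustrate a smaller contrast.** Assume that the comparators carry a share f of the influencer's prestige and that the log odds ratio shrinks in proportion: b(f) = (1−f) × ln 1.81. Then power at N = 327 is Φ[(√327·b − 1.645·√v₀)/√v₁], with v₀ and v₁ recomputed for each b.

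| f (assumed) | Odds ratio | Power at 327 | N for 95% power |
|---|---|---|---|
| 0 | 1.81 | 95% | 327 |
| 0.25 | 1.56 | 79% | 590 |
| 0.50 | 1.35 | 49% | 1,346 |
| 0.75 | 1.16 | 20% | 5,444 |

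For f = 0.50: b = 0.297, v₀ = 10.81, v₁ = 11.08, and (18.08 × 0.297 − 1.645 × 3.288)/3.329 ≈ −0.01, so power is 49%.

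The documents give no value for f. The calculation also keeps the plan's continuous-covariate set-up, so the table shows how sensitive that calculation is to the contrast, not the power of the four-arm comparison.

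**The case against.** **A stronger reading is tempting:** that neither a positive nor a null result could be attributed to prestige. The documents do not support it. If comparators carry some prestige, the contrast shrinks, which mainly harms the reading of a null or reversed result. An influencer advantage is not undermined because the comparators are partly prestigious, and the texts are randomised, so a source effect is identified. What remains for a positive result is narrower: its attribution to prestige is unchecked.

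**A reader might also infer that a positive result could be mere liking,** since Table 1 describes only the influencer as followed and admired. On the plan's own theory, however, prestige promotes admiration and rises with attention, so this description is largely the manipulation itself. The closest family member is hardly low on familiarity, and the plan says that all models are kept in line with the reader's political positions and tastes.

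**The conflict does not extend to all three comparators.** For the family member nothing on the scale is contradicted; the absence of prestige is simply not verified.

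**The supplementary texts and questionnaire are not shown.** The supportable statement is that no prestige rating is among the items the article lists. The trust item and the planned triangulation are a partial proxy.

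**The power figures rest on an assumed share.** Nothing in the documents suggests that the contrast is halved, so a range is the most that can be given.

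What stands after all this is the conflict for the physician and politician, the lack of any listed check, and the ambiguous null.

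**Conclusion.** The point holds in this limited form. The no-prestige statements conflict with the adopted scale for the physician and the politician, and are unverified for the family member. No listed item rates the prestige of the assigned source. Followed as written, the plan could not tell an absent prestige effect from an absent prestige contrast if the result were null or reversed.

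The size cannot be fixed from the documents. Under the assumed shares of 25% to 75%, nominal power in the plan's own calculation falls from 95% to between about 79% and 20%. This rests on a linear link between prestige and the log odds. If a comparator were seen as more prestigious than the influencer, the predicted direction would reverse. The change is worth making, because it is cheap and bears directly on what both hypotheses can conclude.

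**What to change.** 1. After the recall or transmission text has been submitted, add to the existing self-report page a few ratings of the assigned source's status or power, esteem and knowledge, taken from the scale already cited.
2. Ask them in all four arms of the recall stage and of first-generation participants in the transmission stage. Later generations read a predecessor's recall, from which the source may have disappeared; ask them only if the source is still in the text they read, with a *source not mentioned* option.
3. State under Data exclusion criteria that leaving these items blank does not count as abandoning the experiment. Otherwise drop-off on the new items could remove outcome data already given.
4. Report the ratings by arm. Interpret Hypotheses 1 and 2 as prestige effects only against comparators rated lower than the influencer; otherwise limit the conclusion to source type.
5. Replace the two no-prestige statements with *expected to have less prestige, checked by rating*.

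The cost is about a minute more per participant. The ratings come after the outcome text, so they cannot alter what was written.
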